**Table 1 Tab1:**
[figure not shown]
Perioperative outcome parameters and schedule of study visits and follow-up

### Criteria for discontinuation

When a participant’s continuation in the study is judged to be impossible (see below for possible reasons), the principal investigator or subinvestigator will withdraw the participant from the study and specify the date and time of the discontinuation or dropout, the reason for discontinuation or dropout, and the clinical course in the medical record and case report form (CRF). In addition, at the time of the discontinuation/dropout, the principal investigator or subinvestigator will perform necessary tests and assess the efficacy and safety.

Reasons for discontinuation or dropout include:
When the participant requests to withdraw from the study or withdraws consentWhen the participant is found not to meet the eligibility criteria after enrollmentWhen a concurrent disease worsens and further continuation with the study is difficultWhen an adverse event occurs and further continuation with the study is difficultWhen discontinuation from the study is appropriate for other reasons in the opinion of the principal investigator or subinvestigator

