### Study protocol

Patients are informed about the trial by one of our surgeons [name] in the Surgical Oncology outpatient clinic. After receiving information about the trial, all patients have 2 weeks to consider whether to participate. After 2 weeks, the coordinating researcher [name] contacts the patient to see if they would like to make an appointment to provide informed consent. After obtaining informed consent, randomization is performed using a computerized random number generator by a researcher [name] on the eve of the operation. Concealment of allocation is maintained by using sealed opaque envelopes. There is no blinding for the patient, surgeon, or coordinating researcher after the operation because this is difficult in daily practice. After the operation, patients are informed about the allocated treatment. This study is completely funded by the Division of Gastrointestinal Surgery of Kobe University. The patient’s clinical status is assessed, and preoperative testing is performed.

Next, patients undergo the randomized intervention with either nonplacement or placement of a cervical drainage tube. The study began on 26 July 2018. Each patient undergoes follow-up at 2 weeks after surgery to assess primary and secondary outcomes (Table 1).

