#### Reportable adverse events

All adverse events occurring no later than 14 days after the allocated treatment must be reported, irrespective of the causal relationship to the study treatment, and followed up until resolution or up to 4 weeks after the end (or discontinuation) of the study period. All adverse events assessed to be related to the study drug must be reported through to the end of the study period.

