### Sample size calculation

Based on data from our own case series, the rate of Clavien–Dindo grade 2 or higher anastomosis leakage is 5%. Noninferiority is defined as a significant difference in the primary outcome between the two arms of less than 12%. Based on a one-sided type 1 error rate of 2.5% and power of 80%, the sample size needed to exclude a noninferiority margin of 12% for the difference in the proportion of participants reaching the primary outcome is 104 patients. An estimated compensation of 5% for withdrawals was added, resulting in a total of 110 patients, with 55 in each arm. Figure 1 summarizes the final study design.

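### Unblinded investigators may withdraw randomised patients from the study for complications or late-found ineligibility, with efficacy assessed at dropout, so leaks can be lost from the primary comparison

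*Protocol article*

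**What the plan says.** Under Criteria for discontinuation in the protocol article, when a participant's continuation is judged impossible, "the principal investigator or subinvestigator will withdraw the participant from the study". The possible reasons listed go beyond the patient's own request. They include ineligibility discovered after enrolment, a worsening concurrent disease or an adverse event that makes continuing difficult, and any other reason the investigator considers appropriate. The same paragraph adds that "at the time of the discontinuation/dropout, the principal investigator or subinvestigator will perform necessary tests and assess the efficacy and safety".

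Three other sections bear on this:

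- Study protocol: "Each patient undergoes follow-up at 2 weeks after surgery to assess primary and secondary outcomes". It also says that patient, surgeon and coordinating researcher are not blinded after the operation.
- Sample size calculation: "An estimated compensation of 5% for withdrawals was added, resulting in a total of 110 patients, with 55 in each arm". The starting figure was 104.
- Reportable adverse events: "All adverse events occurring no later than 14 days after the allocated treatment must be reported", whatever their cause, with follow-up that can run past discontinuation.

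**The concern.** The comparison is between placing and omitting a drain at one operation. Apart from withdrawal of consent, none of the listed reasons prevents anyone from recording whether the anastomosis leaked within 2 weeks. Even so, the section ends study participation, and the only efficacy assessment it names for a withdrawn patient is the one at dropout. No section says whether the 2-week leak assessment still applies afterwards.

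Leaks could be lost in two ways. A patient withdrawn for another complication may leak later, after the dropout assessment. Or a withdrawn patient, leak included, may simply not be counted, as the inflation for withdrawals suggests.

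The decision rests on judgement by investigators in an open-label trial, and the reasons overlap with the endpoint, because a leak is itself an adverse event. Losing leaks from the nonplacement arm favours a finding of noninferiority. Losing the same fraction of leaking patients from both arms also shrinks the difference.

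**Working it through.** **Inputs from the Sample size calculation section.** Leak rate 5% (one rate is given; it is taken for both arms), margin 12 points, one-sided type 1 error 2.5%, power 80%, 104 raised to 110, 55 per arm. The article does not name the interval for the noninferiority decision. I use the Wald interval because it corresponds to the formula that reproduces the plan's figure, with a second method as a check.

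**1. The plan's own figure.** n per arm = (1.960 + 0.842)² × (0.05 × 0.95 + 0.05 × 0.95) / 0.12² = 7.85 × 0.095 / 0.0144 = 51.8, so 52 per arm and 104 in all. For the allowance, 104 / 0.95 = 109.5 and 104 × 1.05 = 109.2; both round up to 110. The figures reproduce.

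**2. Events and allowance.** Expected leaks are 0.05 × 110 = 5.5, or 2.75 per arm. The allowance is 110 − 104 = 6 patients.

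**3. Effect of one lost leak.** Upper limit = p1 − p0 + 1.96 × √[p1(1 − p1)/n1 + p0(1 − p0)/n0], with 3/55 leaks in the placement arm.

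| Nonplacement arm | Difference (points) | SE (points) | Upper limit (points) | Below 12? |
|---|---|---|---|---|
| 5/55, all counted | 3.64 | 4.94 | 13.3 | no |
| 4/54, one leaking patient not counted | 1.95 | 4.70 | 11.2 | yes |
| 4/55, one later leak missed, patient counted as leak-free | 1.82 | 4.65 | 10.9 | yes |

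With the Newcombe interval this particular example does not change sides (14.7 to 12.7 for 4/54). The neighbouring one does: 4/55 gives 12.4 and 3/54 gives 10.3.

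**4. False noninferiority under assumed losses.** True rates are set at the margin, 17% against 5%, with 55 per arm. Each leaking patient is lost with probability f and removed from numerator and denominator. The probability of declaring noninferiority is found by exact enumeration. The protocol gives no value for f, so the values below are assumptions. In the nonplacement arm 0.17 × 55 = 9.35 leaks are expected, so f of 10%, 20% and 30% means 0.9, 1.9 and 2.8 patients.

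| f | Lost in both arms (Wald) | Lost in nonplacement arm only (Wald) |
|---|---|---|
| 0 | 3.3% | 3.3% |
| 10% | 5.2% | 6.0% |
| 20% | 8.1% | 10.2% |
| 30% | 12.5% | 16.7% |

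The baseline for comparison is 3.3%, since the Wald limit exceeds 2.5% without any loss. A score test with constrained estimates starts at 2.3% and, with loss in the nonplacement arm only, gives 3.8%, 6.3% and 10.2%.

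Equal loss also matters because the observed rate becomes p(1 − f)/(1 − pf). At f = 20%, 17% becomes 0.136/0.966 = 14.1% and 5% becomes 0.040/0.990 = 4.0%, so a true difference of 12 points appears as about 10.

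**The case against.** A reader might infer that the protocol removes withdrawn patients from the primary analysis. It does not say so. That reading comes from the allowance for withdrawals. The analysis set may be defined in a statistical analysis plan or full protocol that is not shown, and its absence from the article is not a fault. Some of the 6 places may also be for patients lost before any anastomosis exists, since randomisation takes place on the eve of surgery. Setting 6 withdrawals beside 5.5 leaks therefore shows how few events there are, not that the two overlap.

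A reader might also infer that the dropout assessment replaces the 2-week one. The text introduces it as an addition and does not call it the last. The general threshold is that continuation is judged impossible, although the listed reasons speak only of difficulty or appropriateness. A leak that itself prompts withdrawal should be seen at dropout. Adverse events are reported to day 14, which matches the outcome window, so many later leaks would be on record.

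Nor is it right that nothing remains to be stopped after surgery. Without signs of leakage the drain stays until postoperative day 7, so stopping the allocated treatment has a meaning in the placement arm. Ineligibility found late has no necessary link to being sicker.

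All of this stands, and it limits the point. What remains is a data-collection rule that the article does state. An analysis plan cannot recover an outcome that was never collected, and no section carries leaks from adverse event reports into the primary outcome. The listed adverse event items also grade severity as mild, moderate or severe, whereas the endpoint needs a Clavien–Dindo grade.

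**Conclusion.** The point holds as a weakness in how the primary outcome is ascertained. Withdrawal from the study at the judgement of unblinded investigators, efficacy assessed at dropout, and an allowance implying that withdrawn patients do not contribute together leave leaks open to being lost. With about 5.5 expected, one lost nonplacement leak can move the upper limit across the 12-point margin (13.3 to 11.2 in the Wald illustration).

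The false-noninferiority rates illustrate fragility and do not forecast bias. They rest on assumed loss fractions, and the highest figures also assume loss in one arm only. The documents do not support saying that the rule will decide the trial's answer. The change is nevertheless worth making, because it removes the exposure at little cost. The sample size of 104, raised to 110, needs no correction.

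**What to change.** Amend Criteria for discontinuation to separate stopping the allocated treatment from leaving the study, and let only withdrawal of consent end outcome collection. The other listed reasons would then no longer end outcome follow-up.

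For every randomised patient who has the anastomosis, record leak status and Clavien–Dindo grade over the full 2 weeks, and analyse the patient in the randomised arm. State that a leak reported under Reportable adverse events is graded and, if grade 2 or higher, counts as a primary event even after an earlier withdrawal. For patients who withdraw consent, repeat the noninferiority analysis with those in the nonplacement arm counted as leaks.

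The cost is a short amendment and one sensitivity analysis. Adverse events already go into the medical record and case report form, so little new collection is needed. The downside is that a few patients found ineligible stay in the primary comparison. The change concerns data collection and counting only; clinical management is untouched.

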### Handling of adverse events at onset

#### Definition of adverse events

An adverse event is defined as any unfavorable or unintended sign (including an abnormal laboratory change), symptom, or disease occurring after treatment has been allocated, whether or not related to the study treatment.

#### Action taken for the participant following onset of an adverse event

When an adverse event is noted, the principal investigator or subinvestigator will immediately perform appropriate treatment and will record the adverse event in the medical record and CRF without discrepancies. In addition, if the adverse event requires treatment, this should be explained to the participant.

#### Reportable adverse events

All adverse events occurring no later than 14 days after the allocated treatment must be reported, irrespective of the causal relationship to the study treatment, and followed up until resolution or up to 4 weeks after the end (or discontinuation) of the study period. All adverse events assessed to be related to the study drug must be reported through to the end of the study period.

#### Procedures for reporting an adverse event following onset

The principal investigator or subinvestigator will record all adverse events occurring during the abovementioned period in the medical record and CRF without discrepancies. The adverse events should be followed up as far as possible until recovery of the participant to the baseline status or no further follow-up is judged to be required.

#### Information to be recorded for assessment of adverse events

The following information is required to be recorded for assessment of adverse events:
Adverse event termDate of onsetDate of outcomeOutcome: resolved/resolving/resolved with sequelae/not resolved/death/unknownAction taken (for the study drug): no change/discontinued/suspended/dose reduction/dose increase/not applicableOther action taken: none/pharmacotherapy/otherSeriousness: nonserious/seriousSeverity: mild/moderate/severeCausal relationship to the study drug: related/not related

### Handling of serious adverse events following onset

#### Definition of serious adverse events

A serious adverse event is defined as any event that:
Results in deathIs life-threateningResults in disability (i.e., dysfunction that interferes with activities in daily living)Results in potential disabilityRequires hospitalization or prolongation of existing hospitalization for treatmentIs serious on the lines of (1) to (5) aboveorIs a congenital disease or anomaly in the offspring

#### Reportable serious adverse events

Reporting is required for all serious adverse events occurring during the study period, as well as serious adverse events occurring no later than 14 days after the end (or discontinuation) of the study and suspected to be related to the study drug.

#### Procedures for reporting serious adverse events

If an adverse event has occurred and is considered to be serious by the principal investigator, the adverse event data should be handled according to the following procedures:
Reporting from the principal investigator to the head of the research institution and the study representative. The principal investigator will report the adverse event data to the head of the research institution and the study representative as soon as possible, irrespective of the causal relationship to the study drug.Action taken upon receipt of additional information. When any additional information is obtained regarding the adverse event, the principal investigator of the research institution involving the adverse event will report the additional information to the head of the research institution as soon as possible.

### Surgical procedures

#### Thoracic procedure

All patients undergo thoracoscopic esophagectomy in the prone position with radical esophagectomy and total mediastinal lymphadenectomy. To permit easy retraction of the trachea, a single-lumen tracheal tube is inserted into the trachea and a blocker is inserted into the right bronchus for one-lung anesthesia before the procedure. The patient is initially placed in the prone position. Six 5-mm or 12-mm ports are inserted into the third intercostal space (ICS) posterior to the midaxillary line, the fifth and seventh ICS on the posterior axillary line, the sixth and eighth ICS on the midaxillary line, and the ninth ICS on the scapular angle line for fine lymphadenectomy, dividing the esophagus, and dividing the azygos arch. The chest cavity is inflated via the ports with carbon dioxide to an insufflation pressure of 6–8 mmHg. The endoscope is usually inserted through the port in the ninth ICS.

#### Abdominal and cervical procedures

The abdominal procedure is performed completely laparoscopically. Gastric mobilization, abdominal lymphadenectomy around the left gastric pedicle and the celiac axis, and excision of the entire isolated thoracic esophageal specimen and dissected lymph nodes through the esophageal hiatus are initially performed. Next, a gastric conduit of 3–4 cm in width is created outside of the wound and raised via the posterior mediastinum. Subsequently, the esophagogastric anastomosis is made in the neck. For three-field lymph node dissection, the cervical nodes are removed through a collar incision.

#### Placement of cervical drainage tube around the cervical anastomosis

Patients assigned to the placement group undergo placement of a 15-Fr silicone drain through the skin near the left cervical incision. The tip of the drain is placed near the anastomosis. If there are no signs of leakage, the drain is removed on postoperative day 7. Anastomotic leakage will be diagnosed by flare of the neck skin, inflammatory response in a blood examination, nature of the drainage fluid, and findings of computed tomography [14].

#### Study device

A 15-Fr BLAKE Silicone Drain (Ethicon, NJ, USA) is placed around the cervical anastomosis in the placement group. The BLAKE Silicone Drain is made of silicone. The entire drain is flexible and has channels along the sides, instead of holes, to facilitate drainage. It is always used with a continuous suction device (J-VAC Suction Reservoir; Ethicon), which creates a closed drainage system. Drainage is very efficient; a larger area is in contact with the tissue as compared with perforated drains, and the fluid is efficiently removed by capillary pressure.

#### Expected adverse events for medical devices

Hemorrhage, pain, and ascending infection may occur in some cases.

#### Safety and adverse event monitoring

Gastrointestinal surgeons and statisticians are responsible for overseeing the progress and safety of the study, including monitoring adverse events, morbidity, and withdrawals from the study. All adverse events are evaluated for severity. Any serious adverse events such as death, disability, and prolonged hospitalization will be recorded on the CRF and reported to the Biological and Medical Ethics Committee of Kobe University Hospital within 24 h. If the number of serious adverse events related to treatment is higher than in our own database or as reported by other authors, patient enrollment will be terminated immediately, and the Medical Ethics Committee will reassess the safety of the trial.

### Outcome measurements

#### Primary outcome

The primary outcome of this study is the percentage of anastomotic leakage events (grade 2 or higher) based on the Clavien–Dindo classification of surgical complications [15].

#### Secondary outcomes

The duration from surgery to oral intake, hospital stay, and type and dose of analgesics used during hospitalization will be assessed.

#### Interim analysis

No interim analysis is planned in this study.

#### Independent Data Monitoring Committee

An Independent Data Monitoring Committee (IDMC) will be established for this study. The IDMC will be formed as an organization independent from the sponsor/investigator, and will consist of at least two members who are specialists and independent of this study. The IDMC will conduct safety monitoring, including comparison of the incidence of adverse events between the test treatment and control and detailed investigation of serious adverse events as necessary, in order to secure the safety of the patients. Based on the safety monitoring results, the IDMC may advise a change to the study design (e.g., change of the inclusion criteria) to reduce the risk of certain adverse events or discuss appropriateness of continuation of the study.

The IDMC will discuss the appropriateness of continuation of the study based on the regular monitoring. On the basis of this discussion, the IDMC will advise the sponsor/investigator on the appropriateness of continuing the study and the appropriateness of publishing the study results.

### Sample size calculation

Based on data from our own case series, the rate of Clavien–Dindo grade 2 or higher anastomosis leakage is 5%. Noninferiority is defined as a significant difference in the primary outcome between the two arms of less than 12%. Based on a one-sided type 1 error rate of 2.5% and power of 80%, the sample size needed to exclude a noninferiority margin of 12% for the difference in the proportion of participants reaching the primary outcome is 104 patients. An estimated compensation of 5% for withdrawals was added, resulting in a total of 110 patients, with 55 in each arm. Figure 1 summarizes the final study design.

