### Statistical analysis

All prospective data will be statistically analyzed using JMP® 11 (SAS Institute Inc., Cary, NC, USA). To evaluate the significance of differences between the two groups, Chi-squared and Fisher’s exact tests will be used as appropriate for categorical variables, and the nonparametric Mann–Whitney *U* test will be used for continuous variables. The significance level will be set at 5%.

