## Discussion

Randomized clinical trials have demonstrated that prophylactic drains do not decrease the incidence of postoperative complications in elective hepatectomy, colectomy, and cholecystectomy [16–19]. In pancreatic head resection, drain removal on postoperative day 4 was shown to be independently associated with a lower incidence of complications, including intra-abdominal infections [20]. Ascending infections along the drain may increase the incidence of pancreatic fistula in patients with long-term drain placement. On the other hand, whether to place a drain near the cervical anastomosis after McKeown esophagectomy remains controversial, even though drains usually are inserted near the cervical anastomosis at most institutions. In 1998, Choi et al. [10] reported a randomized trial to evaluate the role of closed suction drainage for esophageal anastomosis in the neck. In that randomized controlled study of 40 patients with esophageal carcinoma who underwent esophagectomy with an esophageal anastomosis in the neck, half had a neck drain inserted at the end of the operation. The median duration of drainage was 46 h (range 36–88 h). The median amount of drainage was 63 ml (range 15–210 ml). No hematoma or seroma formation occurred in either group. Anastomotic leakage did not occur in any patients. Consequently, the benefits of closed suction neck drainage could not be demonstrated. They concluded that routine use of a neck drain for esophageal anastomosis in the neck is not necessary [10]. However, there were some limitations in that study. First, the number of patients was too small to evaluate the usefulness of a drain for anastomotic leakage as we described in the section on sample size calculation. Second, their cohort might not have been representative of patients who undergo esophagectomy in general because none of the patients had anastomotic leakage; in general, the anastomotic leakage rate in published studies ranges from 1.5% to 21% [21–25]. In the current study, we hypothesize that nonplacement of a cervical drainage tube will lead to a noninferior postoperative anastomotic leakage rate. As a result, we can omit routine placement of a cervical drainage tube which should contribute to reduce cervical pain. Conversely, if a cervical drainage tube does indeed drain the digestive juices when anastomotic leakage occurs, the Clavien–Dindo grade may improve from grade 3 or higher to grade 2. If so, we can confirm the importance of placing a cervical drainage tube around the anastomosis during McKeown esophagectomy. This randomized trial can provide further evidence to support the use or omission of cervical drainage tube placement in patients who undergo McKeown esophagectomy for esophageal cancer.

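### 104 (110) patients follows correctly from the large-sample formula, but at a 5% leak rate the design does not deliver 80% power and 2.5% one-sided error together

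*Protocol article*

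**What the plan says.** All the planning inputs are in the Sample size calculation section of the protocol article.

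- **Event rate:** from the team's own case series, "the rate of Clavien–Dindo grade 2 or higher anastomosis leakage is 5" percent. Only one rate is given.
- **Margin:** "Noninferiority is defined as a significant difference in the primary outcome between the two arms of less than 12" percent, read here as 12 percentage points on the risk difference.
- **Operating characteristics:** "Based on a one-sided type 1 error rate of 2.5% and power of 80" percent.
- **Size:** the number needed "for the difference in the proportion of participants reaching the primary outcome is 104 patients". Then: "An estimated compensation of 5% for withdrawals was added, resulting in a total of 110 patients, with 55 in each arm".

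The formula is not named. For the analysis, the Statistical analysis section says that "Chi-squared and Fisher’s exact tests will be used as appropriate for categorical variables" and that "The significance level will be set at 5" percent, without saying whether this is one- or two-sided. No confidence interval or noninferiority test is named in the article.

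The Discussion adds that "in general, the anastomotic leakage rate in published studies ranges from 1.5% to 21" percent.

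**The concern.** The plan states a pair of properties as if both held at 104 patients: 2.5% one-sided error and 80% power. A normal approximation for a difference of proportions is unreliable when each arm expects two or three events. If the approximation fails, one member of the pair must give way. Either the chance of wrongly declaring noninferiority exceeds 2.5%, or the chance that a truly equivalent no-drain strategy succeeds is below 80%.

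Which one gives way depends on the interval used. With so few events, the choice of interval can decide the result on quite likely data, and the trial is open-label. The power figure and the decision rule should therefore be tied to the same method.

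**Working it through.** **Step 1: reproduce the plan's figure.** Inputs: 5% in both arms (equality is assumed, since one rate is given), margin 0.12, z = 1.960 and 0.842.

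n per arm = (1.960 + 0.842)² × 2 × 0.05 × 0.95 / 0.12² = 51.8, so 52 per arm and 104 in total. For withdrawals, 104 / 0.95 = 109.5, so 110 (55 per arm). Both figures reproduce exactly. The same approximation gives power of 80.2% at 52 per arm and 82.3% at 55.

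**Step 2: expected events.** 52 × 0.05 = 2.6 and 55 × 0.05 = 2.75 leaks per arm.

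**Step 3: exact enumeration.** For every pair of leak counts (0 to n in each arm), declare noninferiority if the upper limit of the two-sided 95% interval for no drain minus drain is below 12% (or the equivalent one-sided test rejects). Sum the binomial probabilities of the successful pairs. Power is taken at 5% versus 5%, and one-sided error on the margin at 17% (no drain) versus 5% (drain).

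| Rule | Power, 52 / 55 per arm | Error, 52 / 55 per arm |
|---|---|---|
| Wald (unpooled) | 80.2% / 80.0% | 3.8% / 3.3% |
| Agresti–Caffo | 72.7% / 78.5% | 2.9% / 3.0% |
| Likelihood ratio | 72.7% / 74.6% | 2.9% / 2.8% |
| Newcombe; Farrington–Manning; Miettinen–Nurminen | 64.7% / 69.6% | 2.15% / 2.33% |
| Wald, continuity-corrected | 64.4% / 70.3% | 1.6–1.8% |

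At a control rate of 1.5%, the Wald error is 5.0% / 5.4%.

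**Step 4: could a better-tuned test rescue the pair?** The score, Agresti–Caffo, Wald and likelihood-ratio statistics were recalibrated so that error is at most 2.5% at a 5% control rate. They then reach at most 72% power (52 per arm) or 75% (55). Held to 2.5% over control rates from 2% to 15%, they reach at most 66% or 71%. Against 80%, the gap runs from about 5 points (80 − 75) to about 15 (80 − 65).

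**Step 5: does the choice matter on plausible data?** Take 3 leaks without a drain and 2 with one, 52 per arm.

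- Difference: 3/52 − 2/52 = 0.019.
- Wald upper limit: 0.019 + 1.960 × √[(0.0577 × 0.9423 + 0.0385 × 0.9615)/52] = 0.101, below 0.12.
- Newcombe upper limit, from the Wilson upper limit for 3/52 (0.156) and lower limit for 2/52 (0.011): 0.019 + √[(0.156 − 0.058)² + (0.038 − 0.011)²] ≈ 0.122, above 0.12.

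The same data pass by one rule and fail by the other. The tables 3 versus 1 and 4 versus 3 split Wald from Newcombe and score in the same way.

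**Step 6: sensitivity to the assumed rate (a separate question).** Newcombe power with equal rates in both arms:

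| Leak rate, both arms | 52 per arm | 55 per arm |
|---|---|---|
| 1.5% | 89% | 89% |
| 3% | 77% | 80% |
| 5% | 64.7% | 69.6% |
| 10% | 47.5% | 51.0% |
| 15% | 38.1% | 40.2% |
| 21% | 33.0% | 34.2% |

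At 10% the Wald rule also gives only 55% / 56%, so most of that drop comes from the rate and not from the formula.

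**The case against.** The strongest reply has four parts.

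**The calculation is right.** 104 and 110 follow from a standard planning formula. This stands. A reader might infer an arithmetic error, but there is none. The weakness is relying on that approximation at this event rate and stating its result as achieved.

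**The interval belongs in the SAP, which is not shown.** It is true that the size of the shortfall depends on the method finally used, so 65–70% is not a fixed property of the trial; it belongs to Newcombe and score intervals. It is also true that Newcombe is not perfectly calibrated: its worst error over control rates from 0 to 30% is 2.8%. But leaving the method to an SAP does not rescue the stated pair, because no method tried delivers both numbers at 52 or 55 per arm.

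**The 5% is well founded.** It comes from the team's own series for this endpoint. The published range in the Discussion carries no Clavien–Dindo grade and includes 5%, so it does not contradict the assumption. This stands. A reader might take power of about one half at 10% leakage as part of the formula's failure. It is not: the stated power is conditional on 5%, and power rises to about 89% at the low end of the range.

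**The harm is speculative.** A reader might infer that a failed noninferiority result would be taken as evidence for the drain. The Discussion's remark about confirming the drain's importance is conditional on the drain actually lowering the severity of leaks. It does not say that failing to show noninferiority would confirm it. That consequence is not claimed here.

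**Conclusion.** The point holds in a limited form. The sample size is correctly computed from the Wald formula, but 80% power and 2.5% one-sided error are not available together at 52–55 per arm and 5% leakage. Keeping 80% means an error of 3.3–3.8%. Keeping about 2.2–2.3% with a Newcombe or score interval means power of about 65–70%. Intermediate methods give 73–79% power at 2.8–3.0% error. Recruiting 55 per arm with no withdrawals does not close the gap.

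This rests on equal 5% rates in the two arms, a 12-point margin on the risk difference, 1:1 allocation, and success defined by the upper limit of a two-sided 95% interval (or the equivalent one-sided 2.5% test). The documents support neither an arithmetic slip nor one fixed power figure that applies whatever the analysis method.

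**What to change.** Keep 110 patients and change the text of the Sample size calculation and Statistical analysis sections.

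1. Name one interval for the risk difference that approximately holds 2.5% one-sided error, for example Newcombe or Miettinen–Nurminen/Farrington–Manning. Use its upper 95% limit against 12% for the noninferiority decision. Fix this before outcomes by arm are examined.
2. Restate the power for that interval: about 65% with 52 evaluable patients per arm, or about 70% with 55, at 5% leakage in both arms. The 104 may stay, described as the result of the large-sample formula.
3. As a separate sensitivity statement, give power on both sides of 5% (52 / 55 per arm): about 89% / 89% at 1.5%, 77% / 80% at 3%, 47% / 51% at 10%, and 38% / 40% at 15%.

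The cost is text only, with a less favourable stated power. For information, the score test stays at or above 80% from about 70 evaluable per arm by enumeration (82.2% power, 2.4% error), and the asymptotic Farrington–Manning formula needs about 74. That is 140–148 evaluable patients in total. The fix does not require this enlargement.
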